### Relevant concomitant care permitted or prohibited during the trial {11d}

This trial does not prohibit other treatments.

### Provisions for post-trial care {30}

After the completion of the interventions, follow-up visits will take place after 3 months, 6 months, and 12 months.

### Outcomes {12}

Primary and secondary outcomes will be assessed at baseline, after the 4-week intervention, and during follow-up visits at 3, 6, and 12 months.

#### Primary outcomes

Pain intensity: Assessed using the Numerical Rating Scale (NRS).

Perceived stress: Evaluated using the Perceived Stress Questionnaire (PSQ).

Quality of life: Measured using the EQ-5D questionnaire.

#### Secondary outcomes

Pain medication consumption: Recorded based on patient self-reporting and medical records.

Biomarkers of stress and inflammation:

Serum cortisol, C-reactive protein (CRP), and interleukin-6 (IL-6) will be measured at baseline and immediately after the 4-week intervention.

### Participant timeline {13}

The participant timeline is given in Fig. 2 The timeline of the whole trial is shown in Fig. 3.

**Fig. 2 Fig2:**
[figure not shown]
Schedule of enrollment, interventions, and assessments.* *t*_3_: 3 months after the intervention, *t*_4_: 6 months after the intervention, *t*_5_: 12 months after the intervention, *t*_6_: 24 months after the intervention

**Fig. 3 Fig3:**
[figure not shown]
Trial timeline flow

### Sample size {14}

Assumptions: To determine the required sample size, we based our assumptions on previous studies investigating similar psychosomatic interventions in patients with chronic pain conditions. We assume the following for the primary outcome (pain reduction):

Effect size: A medium effect size of 0.5 is expected between the intervention groups and the control group.

Significance level (*α*): A two-sided significance level of 0.05 will be used.

Power (1-*β*): To detect a clinically meaningful difference, we aim for a statistical power of 80% (*β* = 0.2).

Drop-out rate: We anticipate a drop-out rate of 15% during the follow-up period.

Sample Size Calculation:

Using these assumptions, we calculated the required sample size using G*Power software for analysis of covariance (ANCOVA), with baseline pain scores as a covariate:

Minimum required participants per group: 30 participants in each group (guided meditation, aromatherapy, and control) are required to detect a medium effect size with 80% power at a significance level of 0.05.

Total sample size: Accounting for a 15% drop-out rate, the total number of participants to be recruited is 104 participants.

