**Methods:**

This is a three-arm, prospective, randomized controlled trial conducted in Germany. A total of 90 participants aged 18 to 90 with chronic musculoskeletal disorders will be randomized into one of three groups: (1) guided meditation, (2) aromatherapy, or (3) control receiving standard care. The intervention groups will receive either body-scan meditation (23 min, twice weekly) or aromatherapy (5–10 min daily) for one week. The primary outcomes include pain intensity (measured using the Numerical Rating Scale), perceived stress (measured using the Perceived Stress Questionnaire), and quality of life (measured using the EQ-5D). Secondary outcomes will include pain medication consumption. Follow-up assessments will be conducted at 3-, 6-, and 12-month post-intervention. Data will be analyzed using an intention-to-treat approach with ANCOVA for primary endpoints.

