## Statistical methods

### Statistical methods for primary and secondary outcomes {20a}

#### Primary estimand

The point estimates for both treatment arms will be presented as mean and standard deviation accompanied by the corresponding 97.5% confidence interval and will be compared between the meditation, the aromatherapy intervention and standard of care. To test the null hypothesis H_0_: μ_diff_ = 0 at a two-sided significance level of 0.025, an analysis of covariance (ANCOVA) with the respective component score at month 6 as dependent variable, treatment arm and center as fixed factor, and pain score at baseline, sex, and age as additional covariates will be used. Results will be presented using estimated marginal means of the difference between both groups accompanied by corresponding 97.5% confidence intervals. The study will be considered as successful if at least one component score shows a significant difference between both treatment arms. Two-sided alpha will be set at 0.025 to adjust for multiple testing.

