### Methods in analysis to handle protocol non-adherence and any statistical methods to handle missing data {20c}

We expect no more than 20% missing values regarding primary endpoints, which are considered to be missing completely at random (MCAR) or missing at random (MAR). To account for missing values regarding primary endpoints, multiple imputation using the Markov chain Monte Carlo (MCMC) method will be used [25]. A sensitivity analysis using an ANOVA approach on ranks will be used to explore the robustness of inference from the initial model.

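### 30 per group for 80% power does not follow from the stated inputs (at d = 0.5 and baseline correlation 0 to 0.7: 48–76% at alpha 0.05, 37–67% at the 0.025 used for testing), and enrolment is given as both 90 and 104

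*Protocol article*

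**What the plan says.** Sample size {14} gives these inputs for pain reduction:

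- Effect: "A medium effect size of 0.5 is expected between the intervention groups and the control group".
- Alpha: "A two-sided significance level of 0.05 will be used".
- Power: "we aim for a statistical power of 80" per cent.
- Method: G*Power, ANCOVA, baseline pain as covariate. No baseline to outcome correlation is given.

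It concludes that "30 participants in each group (guided meditation, aromatherapy, and control) are required to detect a medium effect size with 80% power" and, after a 15% allowance for drop-out, that "the total number of participants to be recruited is 104 participants".

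Two other places bear on this. The primary estimand section under {20a}, which analyses the month-6 score, says "Two-sided alpha will be set at 0.025 to adjust for multiple testing" and plans 97.5% intervals. The abstract's Methods paragraph says "A total of 90 participants aged 18 to 90" will be randomised to the three groups.

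**The concern.** A two-group comparison at d = 0.5, two-sided 0.05 and 80% power is a standard case that needs 64 per group. Thirty is less than half of that, so the gap must come from the covariate, from a different effect measure, or from an error. The section does not say which.

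This is the only quantitative justification for the size of the trial. If it stands, a non-significant result would be reported as coming from an 80%-powered trial when its chance of finding its own target effect may be well below that. The provision in {11b} and {21b} to re-estimate the sample size if recruitment fails would also start from this calculation. The mismatch in alpha lowers the power further. The two enrolment figures leave it unclear whether 30 per arm is the number randomised or the number expected to complete.

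**Working it through.** **Inputs.** From {14}: effect 0.5, two-sided alpha 0.05, power 80%, 30 per group (90 in total), drop-out 15%, 104 to recruit. From {20a}: two-sided alpha 0.025. From the abstract: 90 randomised. The baseline to month-6 correlation r is not stated, so 0, 0.5 and 0.7 are my assumed range.

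**Step 1: the plan's figure, with 0.5 as d.** For one intervention arm against control, the noncentral t test has noncentrality d_eff × √(n/2), with d_eff = d/√(1 − r²) and 90 − 3 − 1 = 86 error degrees of freedom. With n = 30, √(30/2) = 3.873.

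| Assumed r | d_eff | Noncentrality | Power, alpha 0.05 | Power, alpha 0.025 |
|---|---|---|---|---|
| 0 | 0.500 | 1.936 | 48% | 37% |
| 0.5 | 0.577 | 2.236 | 60% | 48% |
| 0.7 | 0.700 | 2.712 | 76% | 67% |

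A plain two-group t test (58 df) gives the same figures to within about one percentage point. The stated 80% is not reached in any row. Solving for r, 30 per arm gives 80% at r of about 0.73 (alpha 0.05) or 0.79 (alpha 0.025).

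**Step 2: n per group for 80% power at d = 0.5.** The ranges reflect two-group or three-arm error df.

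| Assumed r | Alpha 0.05 | Alpha 0.025 |
|---|---|---|
| 0 | 64 | 77–78 |
| 0.5 | 48–49 | 58–59 |
| 0.7 | 33–34 | 40–41 |

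Other variants do not recover 30 either. A one-sided 0.05 test needs 51 per group, and pooling both interventions against control (60 v 30) gives 61% power.

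**Step 3: G*Power's ANCOVA.** This is a noncentral F test with noncentrality f² × N, 3 groups and 1 covariate, at alpha 0.05.

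| f | N for 80%, 2 df | N for 80%, 1 df | Power at N = 90 (2 df / 1 df) |
|---|---|---|---|
| 0.25 (conventional medium) | 158 | 128 | 54% / 65% |
| 0.236 (both arms 0.5 SD from control: 0.5 × √2/3) | 177 | 144 | 49% / 60% |
| 0.50 | 42 | 34 | 99% / over 99% |

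None gives 90. That total corresponds to f of about 0.33 (2 df) or 0.30 (1 df).

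**Step 4: effect detectable with 80% power at 30 per arm.** This is the detectable d at r = 0, multiplied by √(1 − r²).

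- Alpha 0.05: 0.74; × 0.866 = 0.64 (r = 0.5); × 0.714 = 0.53 (r = 0.7).
- Alpha 0.025: 0.81; 0.70; 0.58.

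**Step 5: enrolment.** 3 × 30 = 90, so {14} treats 90 as the number before the drop-out allowance. 90 × 1.15 = 103.5, which rounds up to the stated 104. Dividing instead, 90/0.85 = 105.9, or 106, and 104 × 0.85 = 88.4; that difference is trivial. The abstract's 90 matters more. If only 90 are randomised, 90 × 0.85 = 76.5, or 25.5 per arm. With r = 0, power is then about 42% at alpha 0.05 and 31% at 0.025.

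**The case against.** The strongest reply is that ANCOVA with baseline pain is the stated method, so some positive r is part of the calculation, and a condensed article may leave its value to the full protocol. This stands in part. A reader might infer that no assumptions lead to 30 per group, or that power is simply 48% (or 37%). The document supports neither: r of about 0.73 would give 80% at alpha 0.05, and 48% and 37% are the bottom of a range. The absence of r is not in itself the fault. The fault is that the printed inputs do not yield the printed result, and the value needed would have to hold from baseline to month 6 in a population that the Discussion calls heterogeneous. At the alpha used for testing, it would have to be higher still.

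Second, if 0.5 was entered as f, 90 is over-powered, so under-powering is not unconditional. That is correct, but it conflicts with calling 0.5 medium and does not lead to 90.

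Third, the Discussion concedes that the effect size is uncertain and foresees an interim look with possible sample-size adjustment. Neither makes the calculation right for the effect it assumes.

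A reader might also set the 15% drop-out against "We expect no more than 20% missing values regarding primary endpoints" in {20c}. These do not conflict: the second is an upper bound on missing endpoint values, and a participant who stays in can still have some. Lastly, the plan is intention-to-treat with multiple imputation, so everyone randomised is analysed. The 25.5 per arm is an approximation to the information left, not a count of those analysed.

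**Conclusion.** The concern holds in this form. The 30 per group in {14} is not reproducible from its stated inputs. With 0.5 as d, the likelier meaning of a medium effect between intervention and control, power is 48% to 76% at alpha 0.05 and 37% to 67% at the 0.025 of {20a}, for r from 0 to 0.7. The claimed 80% rests on an unstated r of about 0.73, or 0.79 at 0.025. The alpha mismatch and the 90 versus 104 conflict are in the text and need no assumption. The enrolment conflict is the smaller matter: 90 is 3 × 30, so the abstract probably carries the uninflated number.

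The power figures are per contrast and per outcome. They take 0.5 on the unadjusted standard deviation and credit baseline pain only, not sex, age or centre. The calculation should be corrected before the trial is reported as having 80% power.

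**What to change.** Revise {14} and the abstract, without changing the intended enrolment:

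- Reconcile the alpha in {14} with that in {20a}, and base the calculation on the agreed value.
- State whether 0.5 is d or f, and which baseline to month-6 correlation was assumed.
- Replace the 80% claim with the power that 30 per arm delivers under those assumptions, or with the effect detectable at 80% (Step 4 gives d at each alpha and correlation).
- Give one enrolment figure in both places, making clear whether 90 is the number randomised or the number before the drop-out allowance.

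The cost is wording and a less favourable stated power. No additional participants are needed for the correction.

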### Assignment of interventions: allocation

#### Sequence generation {16a}

Participants will be randomized in a 1:1:1 allocation ratio to guided meditation, aromatherapy, or standard care. The allocation sequence will be generated using a computer-based random number generator (www.randomizer.net) by an independent data management team not involved in recruitment or intervention delivery. Block randomization with randomly varying block sizes (e.g., 6 and 9) will be used to ensure balanced group allocation and prevent prediction of future assignments. Randomization will be stratified by study center to account for potential center effect.

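### The Abstract randomises 90 participants and the sample size section recruits 104; nothing reconciles them, and 90 leaves no allowance for drop-out

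*Protocol article*

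**What the plan says.** The Abstract, under Methods, states: "A total of 90 participants aged 18 to 90 with chronic musculoskeletal disorders will be randomized into one of three groups".

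The protocol's section Sample size {14} gives the per-group requirement as "30 participants in each group (guided meditation, aromatherapy, and control) are required", and then the loss assumption: "We anticipate a drop-out rate of 15% during the follow-up period". It concludes: "Accounting for a 15% drop-out rate, the total number of participants to be recruited is 104 participants".

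Sequence generation {16a} sets equal allocation: "Participants will be randomized in a 1:1:1 allocation ratio to guided meditation, aromatherapy, or standard care".

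Two other sections depend on the target. Criteria for discontinuing or modifying allocated interventions {11b} removes a centre when recruitment at the halfway landmark is under 20% of the overall target. That section and Interim analyses {21b} also provide for re-estimating the required sample size if recruitment fails in more than one centre. Neither section says which total is meant.

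**The concern.** The two totals differ by 14 participants and both describe intake. The Abstract's 90 is the number randomised, not the number expected to finish. It equals 3 × 30, so it treats the minimum required for analysis as the number to enrol and contains none of the drop-out allowance that the sample size section builds in.

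Two things are at stake. First, staff and readers cannot tell when enrolment is complete, and a centre-exclusion threshold set as a fraction of the target has two possible values. Second, if recruitment stops at 90, the trial should expect to miss its own per-group minimum by a clear margin. A lesser question is whether 104 is itself the right allowance for 15% loss.

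**Working it through.** **Inputs**
- Minimum per group 30, so 3 × 30 = 90 (Sample size {14})
- Drop-out 15% during follow-up (Sample size {14})
- Number randomised 90 (Abstract)
- Number to be recruited 104 (Sample size {14})
- Three equal arms (Sequence generation {16a})

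**Step 1: reproduce the plan's 104.** The section does not give its formula. The usual candidates are:
- 90 × (1 + 0.15) = 103.5, rounded up to 104
- 90 / (1 − 0.15) = 105.9, rounded up to 106
- 30 × 1.15 = 34.5, rounded up to 35 per group, total 105
- 30 / 0.85 = 35.3, rounded up to 36 per group, total 108

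Only the first gives 104, so multiplication by 1.15 is a reasonable inference. Recruiting N with a loss fraction of 0.15 leaves N × 0.85, so the number that preserves 90 is 90/0.85.

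**Step 2: expected completers, N × 0.85**

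| Randomised | Completers | Per arm | Against 90 |
|---|---|---|---|
| 90 | 76.5 | 25.5 | −13.5 |
| 104 | 88.4 | 29.5 | −1.6 |
| 106 | 90.1 | 30.0 | +0.1 |
| 108 | 91.8 | 30.6 | +1.8 |

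A target of 104 keeps 90 completers only if drop-out is at most 1 − 90/104 = 13.5%. A target of 90 keeps them only if nobody is lost.

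**Step 3: what the shortfall costs in power.** The plan states "A medium effect size of 0.5 is expected between the intervention groups and the control group" and "A two-sided significance level of 0.05 will be used". It uses ANCOVA with baseline pain as covariate but gives no baseline-to-outcome correlation r, so r is an assumption here. For one intervention arm against control, the normal approximation is

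power = Φ( 0.5 / √(1 − r²) × √(n/2) − 1.96 ).

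| Assumed r | n = 30 | n = 29.5 (from 104) | n = 25.5 (from 90) |
|---|---|---|---|
| 0 | 0.491 | 0.484 | 0.431 |
| 0.5 | 0.609 | 0.601 | 0.540 |
| 0.72 | 0.797 | 0.790 | 0.730 |
| 0.75 | 0.833 | 0.827 | 0.770 |

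A correlation of about 0.72 is what makes 30 per group give roughly 80% power. Across this range, the loss relative to 30 per arm is about 0.007 to 0.008 if 104 are recruited and about 0.06 to 0.07 if 90 are.

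**Step 4: effect on the centre rule.** If its 20% refers to the whole trial's target, the threshold is 0.20 × 90 = 18 or 0.20 × 104 = 20.8 participants, depending on the total used.

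**The case against.** The best defence of the two totals is that they count different things. One version is that 90 is the evaluable number. The Abstract rules that out, because it says the 90 are randomised. Another is that 104 are recruited and 90 of them go on to randomisation. That fails too, because the 15% is placed in the follow-up period, after randomisation. The contradiction stands.

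On the inflation, the other side is largely right. The slip is two participants (four with whole equal arms), the formula is inferred, and the expected shortfall under 104 is about half a participant per arm. Drop-outs also stay in the intention-to-treat analysis with multiple imputation. Imputation does not restore the lost information, however, and the plan itself chose to inflate for drop-out, so reading 30 as completers is fair.

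Three stronger readings may tempt a reader, and the document does not support them:
- **Conflicting attrition rates.** The missing-data section says "We expect no more than 20% missing values regarding primary endpoints". That is a ceiling on missing endpoint values, which can include missed visits or incomplete questionnaires from people who remain in the trial. The 15% is an expected rate of participant drop-out. The two can coexist.
- **104 is incompatible with 1:1:1 because it does not divide by three.** Randomisation is stratified by centre in blocks of varying size across four practices. Incomplete blocks mean that exact thirds are not guaranteed under any total.
- **The enrolment arithmetic explains low power.** It does not. Whether 30 per group gives 80% power depends on the effect size, the covariate gain and the alpha level. With the stated effect size of 0.5, a two-sided alpha of 0.05 and no covariate gain, the same approximation requires 63 per group. That is a separate matter, which neither 106 nor 108 would settle.

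**Conclusion.** The point holds as a contradiction between two stated enrolment totals. Under the plan's 15% drop-out, randomising 90 leaves 76.5 expected completers, 25.5 per arm, which is 15% below the stated minimum. The power cost is about 0.06 to 0.07, using a two-sided alpha of 0.05, a standardised difference of 0.5 and an assumed baseline correlation anywhere from 0 to 0.75. The recruitment end point and the base for the centre-exclusion rule remain ambiguous until one number is chosen.

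The step from 90 to 104 is a minor error. It leaves 88.4 expected completers, 29.5 per arm, and costs less than 0.01 in power. It is worth correcting while the number is being settled, but would not carry the point alone. Both shortfalls are expected values and take the 15% as given.

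**What to change.** State one randomisation target, identical in the Abstract and in Sample size {14}, and make clear that it is the base for the centre rule in {11b}. Then do one of the following:

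- **Correct the inflation:** 90/0.85 = 106, or 36 per arm = 108 if whole equal arms are wanted.
- **Keep the chosen number:** state the completers expected after 15% loss (about 88 for 104, about 76 for 90) and restate the power for that number, giving the covariate correlation assumed.

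If 104 is the operative number and is kept, the Abstract changes by one figure and the sample size section gains a sentence. Correcting the inflation adds 2 participants (106) or 4 (108) to 104; if centres are working to 90, it adds 16 or 18. A change to the protocol itself, as opposed to the article, would also fall under the amendment section {25}, which requires ethics approval and renewed consent. Recruitment is expected to run to about April 2027, so the number should be settled well before then.

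### Sample size {14}: the recruitment total of 104 falls about two patients short of the stated minimum of 30 per group at the stated 15% drop-out

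*Protocol article*

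**What the plan says.** The Sample size {14} section of the protocol article gives three figures that bear on this point.

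- The minimum: "30 participants in each group (guided meditation, aromatherapy, and control) are required to detect a medium effect size with 80% power". Over three groups that is 90.
- The expected loss: "We anticipate a drop-out rate of 15% during the follow-up period".
- The resulting total: "Accounting for a 15% drop-out rate, the total number of participants to be recruited is 104 participants".

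The section does not print the step from 90 to 104. Sequence generation {16a} sets equal allocation: "Participants will be randomized in a 1:1:1 allocation ratio to guided meditation, aromatherapy, or standard care". The abstract gives a different total under Methods: "A total of 90 participants aged 18 to 90 with chronic musculoskeletal disorders will be randomized into one of three groups".

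**The concern.** A drop-out rate is a fraction of those recruited. To end with 90 after losing 15%, the 90 must be divided by 0.85. The stated 104 is lower than that division gives, and it matches the result of adding 15% to the 90. Adding a percentage to the target always falls short of replacing the same percentage lost from the recruits.

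What is at stake is whether the printed total delivers what the same section calls the minimum. The three figures stand together, so this is a stated number that misses its own requirement. It is not a detail left to a fuller document. The point takes the 30 per group and the 15% as given and tests only the step between them.

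**Working it through.** **Inputs**, all from Sample size {14}: 30 per group, three groups, 15% drop-out, stated total 104.

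**1. Reproducing the stated figure.** The candidate calculations are:

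| Calculation | Result | Total |
|---|---|---|
| 90 x 1.15 | 103.5 | 104 |
| 30 x 1.15 per arm | 34.5, so 35 per arm | 105 |
| 90 / 0.85 | 105.9 | 106 |
| 30 / 0.85 per arm | 35.3, so 36 per arm | 108 |

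Of these, only the first gives 104.

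**2. What 104 delivers at 15% loss.** 104 x 0.85 = 88.4 expected completers, and 88.4 / 3 = 29.5 per arm. The requirement is 90, or 30 per arm. The shortfall is 90 - 88.4 = 1.6 expected completers, about half a patient per arm.

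**3. The loss at which 104 would suffice.** 1 - 90/104 = 14/104 = 13.46%, or about 13.5%.

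**4. What the alternatives deliver.** 106 x 0.85 = 90.1 completers in total. 108 x 0.85 = 91.8 completers, or 30.6 per arm. With 106 split 36/35/35, the two smaller arms would expect 35 x 0.85 = 29.75 each. So 106 meets the total of 90, and 108 also meets 30 in every arm.

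**5. Effect on power.** The section gives an effect size of 0.5 and a two-sided level of 0.05, but neither the effect-size metric nor the correlation between baseline and follow-up pain. Here 0.5 is read as a standardized mean difference between two arms, and the correlation is an assumption (normal approximation):

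| Assumed baseline correlation | Power at 30 per arm | Power at 29.47 per arm | Difference |
|---|---|---|---|
| 0 | 49.1% | 48.4% | 0.7 points |
| 0.5 | 60.9% | 60.1% | 0.8 points |
| 0.72 | 79.7% | 79.0% | 0.7 points |

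The loss is under 1 percentage point throughout. The level of power depends heavily on the assumed correlation, but the difference does not.

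**6. The abstract's total.** If 90 were the number randomized, a 15% loss would leave 90 x 0.85 = 76.5 completers, which is further below the minimum than 104 leaves.

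**The case against.** The strongest objection is size. 104 is two patients, or 2/106 = 1.9%, below 106. The 15% is only an anticipated rate, and a modestly lower rate would make 104 sufficient. No decision in the trial turns on the gap. That stands, and it limits the point to a wrong printed figure.

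A second objection is that drop-outs are not discarded. The Drop-outs section keeps withdrawn and lost participants in the intention-to-treat analysis, and the missing-data section {20c} imputes missing primary endpoints. This also stands. A reader might take 88 to be the number analysed, but the documents do not support that: it is the expected number with observed outcomes. Imputation does not restore all the information lost, and the plan itself chose to inflate for drop-out, so the inflation should still be right.

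Three further inferences are tempting and should not be made.

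- **That the plan multiplied by 1.15.** This is a good inference because it reproduces 104, but no formula is printed. The shortfall holds however 104 was obtained.
- **That 104 is wrong because it does not divide by three.** It is stated as a total to recruit. Randomization is stratified by center with varying block sizes, so exactly equal arms are not guaranteed at any total, and 35/35/34 is compatible with 1:1:1 allocation.
- **That center milestones are miscounted.** The discontinuation criteria {11b} refer to the total target without naming a number. Their 20% threshold would be 20.8, 21.2 or 21.6 patients for totals of 104, 106 or 108, a shift of less than one patient.

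**Conclusion.** The point holds as a minor wrong figure. With 30 per group and 15% drop-out, a total of 104 gives 88.4 expected completers against a minimum of 90, and the matching total is 106. The shortfall is two recruits, 1.6 expected completers and less than 1 point of power.

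The conclusion rests on reading 15% as a share of those recruited and 30 per group as the number needed with observed outcomes. The power figures also rest on the assumed metric and correlations shown above.

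A reader might infer that this error leaves the trial materially underpowered, or that correcting it would secure 80% power. Neither follows. The effect of this step is too small for the first. For the second, the check does not test whether 30 per group is itself adequate, and changing 104 to 106 or 108 would not settle that.

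**What to change.** In Sample size {14}, do one of the following.

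- Keep 104 and add that at 15% drop-out it yields about 88 completers, 29 to 30 per arm. This costs one sentence and no patients.
- Restate the total as 90 / 0.85 = 106, or as 36 per arm and 108 in total if equal whole arms are wanted. This costs two or four more patients.

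In either case, print the formula, and reconcile the total with the 90 randomized in the abstract so that the article carries one recruitment target.
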